## Abstract

**Introduction:**

Obesity and associated diseases place a severe burden on healthcare systems. Behavioural interventions for weight loss (WL) are successful in the short term but often result in weight regain over time. Self-regulation of eating and activity behaviours may significantly enhance weight loss maintenance (WLM) and may be effectively augmented by contextual behavioural approaches to emotion regulation. The NoHoW trial tests the efficacy of a theoretically informed, evidence-based digital toolkit using a mobile-enabled website, activity trackers and Wi-Fi scales for WLM aiming to target (1) self-regulation and motivation, and (2) emotion regulation in adults who achieved clinically significant (≥5%) WL in the previous 12 months (initial body mass index (BMI) ≥25 kg/m^2^).

**Methods and analysis:**

The study is an 18-month, 3-centre, 2×2 factorial single-blind, randomised controlled trial, which recruited 1627 participants achieving ≥5% WL between March 2017 and March 2018. Participants are randomly allocated to one of four arms: (1) self-monitoring only (self-weighing and activity tracker), (2) self-regulation and motivation, (3) emotion regulation or (4) combined self-regulation, motivation and emotion regulation. Participants attend four clinical investigation days at 0, 6, 12 and 18 months and are instructed to use the digital toolkit for 18 weeks during the first 6 months and at their discretion for the remaining 12 months. The primary outcome is change in weight (kg) at 12 months from baseline. Secondary outcomes are body composition (eg, bioimpedance analysis), health biomarkers (glycated haemoglobin, lipids, blood pressure, hair cortisol), dietary intake, physical activity, sleep, motivational, self-regulatory, emotion regulatory moderators/mediators of WLM, engagement, user experience, acceptability and cost-effectiveness of the interventions.

**Ethics and dissemination:**

Ethical approval was granted by Institutional Ethics Committees at the Universities of Leeds (17–0082; 27 February 2017), Lisbon (17/2016; 20 February 2017) and Capital Region of Denmark (H-16030495, 8 March 2017). Results will be published in scientific journals.

**Trial registration number:**

ISRCTN88405328.

Strengths and limitations of this studyThe first project to develop and evaluate (via randomised controlled trial) an information and communications technology toolkit combining continuous tracking of physical activity and body weight with theoretically informed, evidence-based digital interventions targeting self-regulation and motivation, and emotion regulation in a 2×2 design, to target long-term weight management.The 2×2 factorial design is a step forward from a conventional two-armed trial to determine the effect of self-regulation/motivation, emotion regulation interventions and their interactions on weight and health outcomes.Analyses of primary outcomes will test the hypotheses that self-regulation of energy balance behaviours improves longer term weight outcomes and that emotion regulation strategies help prevent weight relapse. Moderator analysis will determine if participant psychological/behavioural profiles predict response to self-regulation or emotion regulation interventions. Mediation analyses will examine mechanisms of action by which self-regulation and emotion regulation-based approaches affect energy balance behaviours, weight and health.Participants are blinded to study allocation, but they can access similar interventions from other real-world sources.There was no zero-intervetion control. The active control arm includes self-monitoring of physical activity and weight but the inclusion of the Fitbit devices across all arms potentially contaminates or diminishes the effect of self-regulatory components. Social support was excluded as a potential contaminant of the digital intervention.

## Introduction

Overweight, obesity and associated diseases are key societal challenges. Obesity prevalence accounts for 3%–8% of health costs and 10%–13% of deaths in Europe.^1^ This translates into €59 billion a year in direct, and an estimated €118–€236 billion in indirect, healthcare costs.^2^ These costs are set to rise in parallel with obesity prevalence.^3^ Approximately 40% of the adult population in Europe report engaging in at least one weight control attempt in the previous 12 months.^4^ Existing community-based programme support initial weight loss (WL) but are subject to high attrition or weight regain, limiting longer term effectiveness.^5 6^ The obesogenic environment and asymmetry of human energy balance (EB) regulation facilitates weight gain, while society criticises people suffering from overweight and obesity, leading to stress and negative emotions, which can undermine weight loss maintenance (WLM) attempts.^7 8^ Effective support for WLM or the prevention of weight regain needs to address sustained changes in EB behaviours (dietary, physical activity and weight control) and additional emotional/psychosocial challenges that may undermine planned healthy behaviours.

### Self-regulation and motivation

Core features of effective WLM interventions include behaviour change techniques in line with self-regulation theories such as (1) *self-monitoring* of weight and behaviour; (2) *goal-setting*: agreement of clear weight targets/trigger points for weight control efforts; (3) feedback on behaviour and weight; (4) *action plans* for weight control through dietary and physical activity behaviours; and (5) *plans* to cope with *risk factors* for weight regain and relapse prevention (eg, problem solving).^9–15^ Further, self-determined autonomous motivation has been consistently associated with change in EB behaviours for obesity management.^16 17^ Interventions rooted in Self-Determination Theory may offer a promising approach to sustained EB and weight control.^12 17^ A recent systematic review exploring psychological mediators of sustained effects in diet and lifestyle obesity interventions found that higher levels of autonomous motivation, self-efficacy, self-regulation skills, flexible eating restraint and positive body image were mediators of medium-term to long-term weight control.^18^ The combination of motivational and volitional processes of EB behaviours can contribute to effective WLM; that is, it appears those who are adequately motivated and who implement intentions tend to both initiate and maintain such changes.^19–21^ However, physical activity and dietary interventions based on current behaviour change theories characteristically achieve significant, but small and heterogeneous effects.^22^ Additional psychological processes, such as emotion regulation, can potentially have incremental beneficial effects on the behavioural changes that promote WLM.^23^

### Emotion regulation

Individuals with obesity or those trying to lose weight can experience increased stress, depression, anxiety and weight-related stigma^24 25^ which may undermine weight control attempts. Repeated attempts at WL followed by weight regain can have a negative emotional impact, leading to self-critical thoughts and negative emotions. For some, ‘comfort eating’ may be a means of coping with these negative experiences, potentially derailing strategies of planned behaviour.^26–28^ Relapse prevention models include contextual behavioural (CB)-based emotion regulation strategies such as compassion, acceptance and mindfulness.^29–31^ Evidence suggests that mindfulness and acceptance of undesired internal experiences (eg, negative emotions or self-criticism) and compassion for the self and others may help some individuals adopt adaptive behaviours that are congruent with their weight goals or values.^32–36^ Mindfulness-based interventions show promise in changing obesity-related eating behaviours (eg, binge eating and emotional eating), lowering depression levels and improving WLM.^37^ Augmenting current self-regulatory approaches with CB emotion regulatory approaches could lead to more effective WLM.^32–36^

### Digital behaviour change interventions

Recently, there has been interest in digital interventions to promote and maintain health.^38^ Digital solutions, such as smartphone applications and wearables, can be effective in supporting WLM if they are evidence-based, apply a choice of behaviour change techniques with individualised feedback,^22 39 40^encourage the use of self-regulatory techniques (eg, self-monitoring) and develop intrinsic motivation.^41^ Digital solutions are potentially cost-effective and scalable to large populations, which could engage citizens in healthcare innovations that are convenient and effective for weight management in the face of limited public budgets.^42^ To date, most commonly available weight management applications miss key evidence-based approaches for longer term behaviour change.^43 44^

### Study objectives and hypotheses

The effectiveness of long-term evidence-based digital interventions and strategies to support WLM is limited.^45^ The study’s primary objectives are to evaluate whether using a new digital toolkit is effective for WLM by improving (1) self-regulation and motivation, (2) emotion regulation or (3) these factors in combination, compared with (4) control (generic toolkit content, regular self-weighing and Fitbit use), in 1627 participants at three European centres. We hypothesise that the combined intervention will be more effective for WLM compared with the self-regulatory or emotion regulatory interventions alone, which will also be more effective than the control group.

Secondary objectives are to determine (1) how the intervention affects health markers (eg, levels of glycated haemoglobin (HbA1c)) and body composition; (2) examine the intervention impacts on physical activity, sleep, dietary intake, depression, anxiety, stress, quality of life and well-being; (3) examine mediators of WLM, such as self-regulation (eg, planning capacity), motivation (eg, autonomous motivation) and emotion regulation processes (eg, self-compassion); (4) analyse baseline moderators (eg, gender, body mass index (BMI)) to identify participants who are more responsive to motivational and behavioural self-regulatory or CB-emotion regulatory approaches for WLM; (5) conduct quantitative and qualitative assessment of user-experience, acceptability, engagement and dropout; (6) examine intervention cost-effectiveness; and (7) to determine the efficacy of individualised feedback from data on physical activity self-tracking.

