### Interventions

The toolkit is a mobile-enabled website, delivered as a portfolio of embedded tracking technologies, mini-apps and web resources (figure 2) accessible via computer, tablet and mobile phone. The tracking technologies consist of an activity and sleep tracker (Fitbit Charge 2) and smart wireless body weight scale (Fitbit Aria). Participants were asked to wear the Fitbit Charge 2 at all times and to weigh themselves ≥twice weekly. All arms include instructions for self-weighing and use of activity trackers. Arms 2 and 4 include individualised weekly feedback about weight trajectories. Guidance for complex interventions was followed during the toolkit development specifying the intervention logic models and theory-driven behaviour change techniques,^50^ which will be detailed in a separate publication.

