#### Arm 1 (active control, self-monitoring, only)

The active control arm includes a toolkit dashboard containing weight, steps and sleep graphs using data from the Fitbit devices, healthy eating and mood data (self-scored on a five-point scale), a diary to populate with notes from these five tiles and a help tile. The content is generic and does not relate to any theoretically informed, evidence-based behaviour change approaches.

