#### Arms 2–4

After randomisation, participants received standardised training from researchers during the first CID, specific to their arm allocation. Trial arms 2–4 include the same components as arm 1 but participants also receive a personal virtual road map (the ‘NoHoW Journey’) with intermediate destinations represented in that map by circles, each comprised of evidence-based theoretically informed thematic modules targeting self-regulation and motivation (arm 2), emotion regulation (arm 3) and combined self-regulation and emotion regulation (arm 4). Arm 4 includes the same number of thematic modules as arms 2 and 3. Each weekly module opens into submodules. The active intervention involves 18 weekly sessions delivered throughout a 6-month period. Users are encouraged to complete ≥1 submodule per week following the sequence in the road map, consisting of videos/audios, interactive graphs, text, images, questionnaires and mini-apps. Weekly arm-specific emails are sent during the active 6-month intervention phase, which provide WLM information, suggestions and reminders to visit specific content. The toolkit automatically sends an email notifying participants to slow down if they complete three sessions ahead of schedule. After 6 months, they are encouraged to revisit the toolkit for a further 12 months at their discretion.

Individualised feedback is a component of the self-regulation and motivation arms (arms 2 and 4) automatically provided by the toolkit in response to the individual’s weight trajectory. Feedback is generated from the data extracted from three sources: (1) weight from the Fitbit Aria scales; (2) activity and sleep from the Fitbit Charge 2; and (3) user engagement with the toolkit, including day of the week. After daily usage patterns are analysed, feedback is displayed in the toolkit consisting of one of a set of short statements (eg, “your weight management appears better when you are more active”).

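### Secondary objective 7 promises the efficacy of individualised feedback, but feedback comes only bundled with the self-regulation and motivation modules, so no randomised contrast isolates it

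*Protocol article*

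**What the plan says.** In the Protocol article, Study objectives and hypotheses, the last of seven secondary objectives is "to determine the efficacy of individualised feedback from data on physical activity self-tracking".

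The intervention text settles who receives feedback. Under Interventions: "Arms 2 and 4 include individualised weekly feedback about weight trajectories". Under Arms 2–4: "Individualised feedback is a component of the self-regulation and motivation arms (arms 2 and 4) automatically provided by the toolkit", and it is issued "in response to the individual’s weight trajectory". That subsection names three data sources: scale weight, tracker activity and sleep, and engagement with the toolkit. It also describes the thematic modules: self-regulation and motivation in arm 2, emotion regulation in arm 3, both kinds in arm 4. Arm 4 has the same number of modules as arms 2 and 3.

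Self-tracking itself does not differ by arm: "All arms include instructions for self-weighing and use of activity trackers". The control arm has a "toolkit dashboard containing weight, steps and sleep graphs using data from the Fitbit devices", with no feedback statements described. The article describes one randomisation, to four arms.

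**The concern.** To determine efficacy is a causal aim, and in a randomised trial a reader will expect a randomised comparison behind it. Here none exists for feedback on its own. No arm has the modules without feedback, and none has feedback without the modules.

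If the objective stands as worded, one of two results could be reported under it. One is the effect of the whole self-regulation and motivation package under the name of feedback. The other is a non-randomised association within arms 2 and 4 presented as efficacy. Either could mislead someone deciding whether to build feedback into a later tool, and the article says its secondary analyses are meant to inform more personalised interventions.

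**Working it through.** **Inputs.** Arm composition comes from Interventions, Arm 1 and Arms 2–4. The effect size, power and sample size come from Power calculations and sample size estimation.

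**The plan's own figure.** For d = 0.25, two-sided 5% (5% is stated for HbA1c; two-sided is assumed) and 80% power, the two-group formula gives 252 per arm against the stated 250. Power at 250 per arm is 79.8%. The sample size reproduces, and the point does not rest on it.

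**Step 1: 0/1 coding.** Over arms 1 to 4:

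| | Arm 1 | Arm 2 | Arm 3 | Arm 4 |
|---|---|---|---|---|
| Self-regulation (SR) | 0 | 1 | 0 | 1 |
| Emotion regulation (ER) | 0 | 0 | 1 | 1 |
| Feedback (FB) | 0 | 1 | 0 | 1 |

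The correlation of SR and FB is 1. The model with intercept, SR, ER and SR×ER has rank 4, and still 4 after FB is added. The main-effects model has rank 3, and still 3 with FB.

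**Step 2: what the randomised contrasts estimate.** Let s, e and f be the effects of SR modules, ER modules and feedback, and i the interaction. The arm means are m, m+s+f, m+e and m+s+e+f+i. Then:
- arm 2 − arm 1 = s + f
- arm 4 − arm 3 = s + f + i
- mean of arms 2 and 4 − mean of arms 1 and 3 = s + f + i/2

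Only the sum s + f ever appears. That joint effect is well estimated: about 97.7% power for d = 0.25 with 500 per side.

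**Step 3: module dose instead of 0/1.** Arm 4 cannot hold both full module sets, since it has as many modules as arm 2 or arm 3. Assume a share w of its modules is self-regulation and 1 − w emotion regulation; the article does not give w. With linear, additive dose effects:

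arm 4 − arm 1 = w·s + (1 − w)·e + f, so f = [μ4 − w·μ2 − (1 − w)·μ3] / (1 − w).

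- w = 0.25: f = 1.33μ4 − 0.33μ2 − μ3
- w = 0.50: f = 2μ4 − μ2 − μ3
- w = 0.75: f = 4μ4 − 3μ2 − μ3

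At w = 0.50 the dose column is (0, 1, 0, 0.5). Its correlation with feedback is 0.75/√0.6875 = 0.90, and the additive model has rank 4. So feedback is formally estimable, but the estimand changes with w, and any interaction is absorbed into f. Adding an interaction gives five parameters for four arm means, and the aliasing returns.

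It is also imprecise. With the implied SD of 1.5/0.25 = 6 kg and 250 per arm, the standard error at w = 0.50 is 6 × √(6/250) = 0.93 kg. For an ordinary two-arm difference it is 6 × √(2/250) = 0.54 kg.

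**Step 4: within arms 2 and 4.** Feedback depends on the participant's weight, activity, sleep and engagement. Who gets which message, and how much is seen, follows from earlier values of the outcome and from adherence, not from allocation.

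**Step 5: counting arm 1's graphs as feedback.** Every arm would then have feedback, and there would still be no contrast.

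**The case against.** Bundling is deliberate and coherent. The Introduction lists feedback among the core self-regulation techniques, and the intervention text calls it a component of those arms. This stands: the design is sound for its main purpose, and the fault lies in the wording of one objective.

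Complete aliasing is a result of 0/1 coding. This stands as a limit on the claim. A reader might infer that the design carries no information on feedback at any sample size under any model, and Step 3 shows that is too strong. The escape is not credible as an efficacy test, however. It must assume away the interaction, although the article hypothesises that the combined arm does better than either single one and sets out to study interactions.

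The inputs to feedback are all recorded, and toolkit details are left to other publications, so a careful within-person analysis might be possible. That cannot be ruled out from the article. It would still be non-randomised.

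The analysis of this objective may sit in a fuller document, so the silence of Data analysis on a feedback contrast carries no weight. But an analysis plan cannot create a contrast that was not randomised.

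A reader might also infer that the objective (feedback from activity data) contradicts the intervention text (feedback about weight trajectories). The documents do not support that. One phrase names a data source and the other a topic. Arms 2–4 lists activity data among the sources, and its example message relates weight management to being active.

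**Conclusion.** The point holds. As worded, objective 7 claims an efficacy finding that no randomised comparison in this trial can supply. With the arms coded as the 2×2 factors, the aliasing of feedback with the self-regulation factor is complete. Dose coding lifts it only under three assumptions the article does not support: a known module split, linear dose effects and no interaction. The conclusion rests on the arm composition as published and on there being no separate randomisation of feedback; none is described.

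The reach is narrow: one of seven secondary objectives. The primary outcome, sample size, randomisation and factorial analysis are untouched, and the article makes no feedback claim beyond the objective itself.

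**What to change.** Restate objective 7 in one of two ways:

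1. As the joint effect of the self-regulation and motivation package, including individualised feedback, estimated by arms 2 and 4 against arms 1 and 3.
2. As an exploratory, non-randomised description, within arms 2 and 4, of the association between feedback exposure and later behaviour and weight.

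In either case, state that the randomised contrasts (arm 2 against 1, arm 4 against 3, and the two pooled) estimate modules and feedback jointly.

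The cost is the wording of one objective and one added sentence. Conduct, data collection and sample size do not change. The trial gives up only a claim that its design cannot support.

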## Methods

### Trial design and setting

The NoHoW trial is a three-centre (University of Leeds (UK), The Parker Institute (Denmark) and University of Lisbon (Portugal)) 2×2 factorial, randomised, single-blind, controlled trial testing the proof-of-concept of a digital toolkit for WLM. The study duration is 18 months with a follow-up at 6, 12 and 18 months postbaseline (figure 1). The study is conducted between March 2017 and September 2019 in academic research institutes. In total, 1627 participants (~542 per centre) were enrolled and randomised into one of four intervention arms: (1) active control arm (consisting of generic toolkit content, self-weighing and activity trackers, only); (2) self-regulation and motivation arm; (3) emotion regulation arm; and (4) combined motivation/self-regulation and emotion regulation arm (figure 1). The protocol is harmonised across trial centres using Good Clinical Practice guidance, research-grade translation/backtranslation of trial materials, two training workshops and weekly trial management meetings. The trial registration data set is displayed in table 1. The final protocol (V2.1 20/09/2017) was approved by the Trial Steering Committee (TSC) and adheres to the Standard Protocol Items: Recommendations for Interventional Trials guidelines.^46^

**Figure 1 F1:**
[figure not shown]
Trial design. RCT, randomised controlled trial.

**Table 1 T1:** WHO trial registration data set

Data category	Information
Primary registry and trial identifying number	ISRCTN: 88 405 328
Date of registration in primary registry	16/12/2016
Secondary identifying numbers	H2020-EU.3.1 Grant agreement ID: 643 309
Source(s) of monetary or material support	European Commission, Horizon 2020—EU Framework Programme for Research and Innovation
Primary sponsor	University of Leeds, Leeds, UK
Secondary sponsor(s)	The Parker Institute, Copenhagen, Denmark University of Lisbon, Lisbon, Portugal
Contact for public queries	[name] ([contact]) School of Psychology Faculty of Medicine and Health University of Leeds [name] UK [name]
Contact for scientific queries	[name] ([contact])
Public title	NoHoW: Evidence-based ICT tools for weight loss maintenance
Scientific title	A 2×2 randomised controlled trial to evaluate the effectiveness of evidence-based ICT behaviour change tools for weight loss maintenance in overweight/obese adults after clinically significant weight loss.
Countries of recruitment	University of Leeds (UK). The Parker Institute (Denmark). University of Lisbon (Portugal).
Health condition(s) or problem(s) studied	Adults aged 18 or older who have intentionally lost at least 5% of their body weight in the last 12 months, and initially had a BMI of 25 or more.
Intervention(s)	Participants are assigned to one of four interventions: Self-monitoring only (self-weighing and activity tracker). Self-regulation and motivation. Contextual behavioural science-based emotion regulation (CBS-emotion regulation). Combined self-regulation, motivation and CBS-emotion regulation.
Key inclusion and exclusion criteria	Inclusion criteria: Aged 18 years or older. BMI (prior to weight loss) of ≥25 kg/m^2^. Verification of ≥5% of weight loss in the last 12 months and remain 5% below their highest weight. Ability to use a smartphone and have access to smart phone, tablet or computer with internet access and Wi-Fi. Ability to use standing scales for weight measurements and must not be over 150 kg (the scale limit 158 kg) Exclusion criteria: Inability to give informed consent. Lost weight due to illness or surgical procedures, including bariatric procedures. Pregnant or breastfeeding. Involvement in another research intervention study that confound with the aims of NoHoW (excluding local health interventions and weight management services). Inability to follow written material or telephone conversations in the English, Danish or Portuguese language (depending on the centre). Diagnosed with an eating disorder (eg, anorexia nervosa, bulimia nervosa or purging disorder). Diagnosed with any condition that may interfere with increasing mild to moderate physical activities and which is unstable (ie, untreated or unable to be controlled by medication). Recent diagnosis with type 1 diabetes. Extensive planned travel, that is, moving away or long-term travel abroad (eg, more than 4 weeks). Living in the same household as existing participant in the trial.
Study type	Interventional, 2×2 factorial randomised controlled trial.
Date of first enrolment	20 March 2017
Target sample size	1600
Recruitment status	Completed (31/03/2018), no longer recruiting.
Primary outcome(s)	Weight (kg)
Key secondary outcomes	Body composition: (eg, fat mass and fat-free mass) and waist/hip ratio. Biomarkers: blood pressure, heart rate, cortisol (hair samples), HbA1c, cholesterol. Behavioural: physical activity, sleep and dietary intake. Psychological moderators and mediators of change for: self-regulation and motivation (eg, action planning and coping, self-efficacy); CBS-emotion regulation (eg, weight focused self-criticism, five dimensions of mindfulness); stress management (eg, perceived stress scale, depression, anxiety and stress); and quality of life and well-being. Process evaluation Cost-effectiveness analysis

BMI, body mass index; ICT, information and communications technology.

